## Participant sampling and selection

The PiCTuRE study will be promoted across various digital platforms, including social media, charity websites, and patient support sites, using posters and e-flyers. Given the rarity of the target population, a multistage purposeful random sampling method [42] will be employed to encourage enrolment and identify individuals interested in participating in online semi-structured interviews, collaborating on the co-design of the digital platform, and providing feedback during the testing phase. Recognising the lack of inclusivity in research involving diverse populations, recruitment may also be supplemented through snowball sampling [43] via social media networks and outreach to ethnic community groups. Participants will receive the study information upon clicking the link provided in the online advertisements. An overview of the inclusion and exclusion criteria for all three phases of the study is outlined in Table 1.

**Table 1 Tab1:** Overview of inclusion and exclusion criteria for phases 1 to 3

Inclusion Criteria	Exclusion Criteria
Proficiency in speaking and understanding English	Inability to communicate effectively in English
Aged 18 years or older	Under the age of 18 years old
Lived experience of having a primary tumour of the brain or spine	Unable to provide informed consent
Capable of providing informed consent	No access to internet-enabled devices (e.g., smartphone, tablet, computer)
Able to communicate via digital media	Unable to communicate using digital media
Access to an internet-enabled device (e.g., smartphone, tablet, computer)	

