### Barriers to tissue donation for research

The inherent vulnerabilities experienced by cancer patients often present substantial obstacles to tissue donation for research purposes [18] Several factors contribute to this hesitation among individuals living with tumours. Trust issues frequently arise, with concerns about how donated samples will be used and whether personal data will be adequately protected [19, 20] Clinical time pressures also play a significant role, as limited consultation time often precludes thorough discussions about tissue donation, leaving patients’ questions and concerns unaddressed [21]. Additionally, psychological, and social barriers can deter participation. These include fear of the unknown, such as uncertainties regarding the implications or risks of donation [21] stress and anxiety stemming from the emotional toll of their diagnosis, which can overwhelm patients and reduce their willingness to consent [22]; and a loss of confidence in the healthcare system, resulting from a diminished sense of agency or trust due to their illness experience [23]. Collectively, these barriers highlight the need for tailored approaches to engage and support patients in the donation process.

While existing studies have explored cancer patients’ general attitudes toward biobanking [19, 23, 24], there remains a critical gap in understanding the lived experiences of individuals diagnosed with primary brain or spinal tumours and their specific perspectives on tissue donation.

We suggest that the primary obstacle to advancing translational neuroscience research is not a lack of willing participants but rather the absence of effective engagement strategies, tailored communication, and appropriately timed consent processes.

Addressing these gaps is essential to ensuring access to high value biological samples, which are often removed during routine NHS procedures but remain underutilised due to barriers in the consent process. By fostering better engagement and trust, the potential for transformative research in precision oncology can be fully realised.

**PiCTuRE-** is an exploratory sequential mixed-methods study [25]. Its primary aim is to optimise support for complex patient cohorts in their decision-making processes regarding tissue donation for research through development of a digital consent platform.

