### Phase 1: explore

Underpinned by a scoping review, Phase 1 of the PiCTuRE study will focus on understanding key themes related to the lived experiences of individuals with primary brain or spinal tumours who donate tissue for research.

The explore phase includes two stages of qualitative data collection: an online survey (Phase 1a) and semi-structured interviews (Phase 1b).

In **Phase 1a**, qualitative descriptive data will be gathered through an anonymous online survey distributed via social media and charity websites. Participants will receive study information through an embedded link in the participant information sheet before completing the survey. Consent will be obtained using a tick-box system. The survey is designed to take no longer than 15 min. A copy of the survey questions can be found in the supplementary information file.

Participants who wish to take part in **Phase 1b** will provide additional consent by sharing their email addresses for follow-up within 3 to 6 months. This stage involves online interviews conducted via Microsoft Teams with individuals who consented during Phase 1a. The interviews, lasting up to 45 min, will focus on gaining deeper insights into participants’ experiences. Consent will be documented by the researcher, and all interviews will be recorded with participant approval to support thematic analysis.

The qualitative data collected during Phase 1 will contribute to the development of a digital consent platform for tissue donation, identifying contextual factors that may influence the intervention’s outcomes [30]. The platform aims to provide personalised, tailored, and interactive support to assist patients in making informed decisions regarding tissue donation for research and participation in associated clinical trials. Thematic analysis [31, 32] will guide the refinement of the intervention and validate items for use in the subsequent mixed-method approach. Additionally, this process will provide critical insights into patients’ attitudes toward digital technology, supporting the study’s aim to enhance patient empowerment and engagement.

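### The sampling is labelled purposeful random, but the recruitment described is online self-selection, so the margin-of-error basis for n = 45 does not apply and findings describe digitally able volunteers only

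*Protocol article*

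**What the plan says.** The section on participant sampling and selection says that, because the population is rare, "a multistage purposeful random sampling method [42] will be employed to encourage enrolment and identify individuals interested in participating" in interviews, co-design and testing. The same section says the study is "promoted across various digital platforms, including social media, charity websites, and patient support sites, using posters and e-flyers". It describes entry as follows: "Participants will receive the study information upon clicking the link provided in the online advertisements". Snowballing through social networks and outreach to ethnic community groups are mentioned as a possible supplement, for the sake of inclusivity.

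Phase 1a is "an anonymous online survey distributed via social media and charity websites". Phase 1b takes survey respondents who leave an email address, and Phase 1b participants are then invited to review the tool in Phase 2.

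Table 1 applies to all three phases. It excludes people without an internet-enabled device and anyone "Unable to communicate using digital media". The Phase 1 section nevertheless says that "this process will provide critical insights into patients’ attitudes toward digital technology".

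The sample size section derives 45 survey participants from a 95% confidence level, a 5% margin of error, a proportion of 3% and a population of 67 million.

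**The concern.** The word random claims a property that the described recruitment does not have. A purposeful random sample needs a pool of eligible people and a chance draw from it. An open advert has no list of people and no selection probabilities, because respondents select themselves.

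Two consequences follow.

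- **The sample size justification.** It borrows a margin of error that only a probability sample can carry. A reader could attach plus or minus 5 points to survey percentages that have no such precision.
- **Entry is related to what is studied.** The introduction lists distrust, anxiety and lost confidence in healthcare as barriers to donation. People held back by these may be the least likely to answer a research advert. The general design section describes the group of interest as people weighing up donation or who have already donated, and does not name those who refused. People who cannot use digital media are excluded outright, so their attitudes to digital tools cannot be heard.

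If the report does not say so, the platform could be built on the views of engaged, online patients and presented as fitting patients in general.

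**Working it through.** **1. Reproducing the 45.** Inputs from the sample size section: z = 1.96 (95%, two-sided), p = 0.03, margin e = 0.05, N = 67 million.

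n = z² p(1−p)/e² = 1.96² × 0.03 × 0.97 / 0.05² = 44.7. The finite population correction n/(1 + (n−1)/N) leaves this unchanged. Rounded up, it gives 45, so the figure reproduces. The formula is that of a simple random sample.

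**2. The described entry routes, stage by stage.**

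| Stage | How people enter | Random step described? |
|---|---|---|
| Phase 1a | Click an open advert; possible referral | No |
| Phase 1b | Survey respondents who leave an email address | No |
| Phase 2 | Phase 1b participants invited | No |
| Phase 3 | No separate route given | No |

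The margin in step 1 therefore has no basis in the Phase 1a recruitment. Even for a random sample, 45 people give 5 points only near p = 3%. The half-width 1.96 × √(p(1−p)/45) is 14.6 points at p = 50%, 11.7 at 80% and 8.8 at 90%.

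**3. How large could selection bias be?** The documents give no inputs, so everything here is assumed. Let P be true willingness to donate and k the number of times as likely a willing person is to take part as an unwilling one. The observed share is Pk/(Pk + 1 − P). For P = 60% and k = 2 this is 1.2/(1.2 + 0.4) = 75%, an error of +15 points.

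| True P | k = 0.5 | k = 1 | k = 1.5 | k = 2 | k = 3 | Random-sample half-width, n = 45 |
|---|---|---|---|---|---|---|
| 50% | −16.7 | 0 | +10.0 | +16.7 | +25.0 | 14.6 |
| 60% | −17.1 | 0 | +9.2 | +15.0 | +21.8 | 14.3 |
| 70% | −16.2 | 0 | +7.8 | +12.4 | +17.5 | 13.4 |
| 90% | −8.2 | 0 | +3.1 | +4.7 | +6.4 | 8.8 |

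Errors are in percentage points. The bias may exceed the sampling error or fall below it, depending on P and k. It does not depend on n.

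**4. Digital exclusion.** Let u be the share of patients excluded as offline, and a and b the shares with a positive digital attitude online and offline. The overstatement is a − [(1−u)a + ub] = u(a − b). With assumed u = 5% to 20%, a = 80% and b = 20% to 40%, it runs from 0.05 × 0.40 = 2 points to 0.20 × 0.60 = 12 points. It is 0 if the two groups do not differ.

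**The case against.** The strongest reply is that this is mainly a qualitative study whose objective is to design a tool. Volunteer samples are accepted for that purpose, and the descriptive statistics are there to give context to themes. Digital access matches an online study of a digital platform, and Table 1 states the restriction openly. The method is called multistage and cites a source, so a draw from opt-ins could take place later, when up to 45 respondents feed up to 10 interviews. A condensed article may leave such mechanics to the full protocol.

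Much of this stands. A later random draw is not ruled out, and volunteer sampling is not itself a fault. But the article attaches the label to encouraging enrolment, and no later draw would make the Phase 1a survey random. The reply also does not explain the margin-of-error calculation. The article goes beyond themes as well: it plans comparisons across demographic and clinical segments, correlation analysis, an assessment of the tool's effectiveness, and evidence towards a new standard for cancer consent.

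A reader might go further and infer that willingness to donate is biased upward by design, so that the survey is bound to confirm the introduction's view that the main obstacle "is not a lack of willing participants but rather the absence of effective engagement strategies". The documents do not support this. Table 1 admits people who declined or were never asked, and people with bad experiences may volunteer too. No willingness proportion is defined as an outcome, and the sentence in the introduction is a suggestion, not a hypothesis assigned to the survey. Nor can the sample be called a snowballed one, since snowballing is only a possible supplement.

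**Conclusion.** The point holds in limited form. The recruitment described for Phase 1a is open, online and self-selected, and no random step is described at any stage. The 95% and 5-point basis for 45 therefore does not apply to it, although the arithmetic is correct. Findings on donation and on digital attitudes come from digitally able volunteers. They are plausibly, but not demonstrably, favourable to both.

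The size of any bias cannot be derived from the documents. The illustrative ranges (−17 to +25 points for willingness, 0 to 12 for digital attitudes) rest wholly on assumed inputs and include zero. This is a matter of correct description and scope of inference, and it can be repaired without redesigning the study.

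**What to change.** - **Label.** Describe Phase 1a as self-selected convenience sampling with optional snowballing. Use the word random only for a stage where a draw from opt-ins is actually made, and say how it is made.
- **Scope.** State that survey percentages describe respondents only and carry no population margin of error. Keep 45 as a practical ceiling, not a precision target. State that findings on digital attitudes apply to digitally able patients.
- **Phase 1b selection.** Choose the up to 10 interviewees from opt-ins by maximum variation. Aim, where opt-ins allow, to include people who declined or were never asked, both brain and spine tumours, and under-represented ethnic groups. These should be targets: the introduction puts primary spinal tumours at fewer than 120 a year in the UK, and fixed minimum places within 10 interviews might not be filled.

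The cost is narrower claims, somewhat slower interview selection, and targets that may be missed. A few characteristics would have to be collected with the opt-in email and held apart from the anonymous survey, which may need an ethics amendment.

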### How is personalised complex oncology care evolving??

Historically, individuals undergoing complex oncology surgeries were seldom invited to participate in research related to their condition, with the decision to offer research opportunities often made solely by the treating clinician [14]. However, recent advancements in cancer care have shifted from a traditionally paternalistic approach to a more person-centred, personalised model, emphasising shared decision-making and patient involvement [15].

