### General design

PiCTuRE is a multistage, online, exploratory sequential mixed-methods study [25] aimed at examining the lived experiences of individuals with primary craniospinal tumours who are considering or have donated tissue for research. This design aims to address gap in current published literature by integrating qualitative and quantitative data to explore the complex behaviours within the oncology setting, providing a robust foundation for outcomes.

The qualitative phase delves into motivations and barriers to tissue donation, with insights informing the quantitative phase to ensure relevance and accuracy. By triangulating data, the study enhances the validity and reliability of findings. A diagrammatic overview of the general study design, produced using a mixed methods procedural chart [27] can be seen in Fig. 1.

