### Phase 3: test

Phase 3 of the PiCTuRE study will evaluate the newly co-designed, interactive, personalised digital consent platform, aiming to promote patient autonomy, shared decision-making, and personalised consent. Outcomes will be measured through both qualitative and quantitative methods, with a focus on user experience. Post-intervention, a survey and semi-structured interviews will be conducted to assess participant feedback and explore their lived experiences, including their views on discussing tissue donation for research with healthcare professionals. This phase will provide insights into the effectiveness of the intervention, with Patient Reported Experience Measures (PREMs) used to gather data on satisfaction and engagement [39, 40]. The qualitative data will help validate the quantitative findings and assess the overall success of the intervention [41]. Additionally, user feedback from post-intervention interviews will be analysed for statistical significance, contributing to the refinement of the intervention, and providing evidence for a potential new standard of care in cancer patient consent processes.

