## Data analysis

### Phase 1a

The findings from the online cross-sectional survey will be reported in alignment with the Consensus-Based Checklist for Reporting of Survey Studies (CROSS) [44]. Thematic analysis [31] be employed to examine open-ended responses, identifying key themes and patterns. Recurring codes and themes will be subjected to comparative analysis across demographic and clinical segments, such as age groups, gender, and diagnosis. Descriptive statistics will be utilised to contextualise the themes generated through qualitative analysis. Additionally, correlation analysis will be conducted to explore relationships between variables.

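### Phase 3 testers need never have faced a tissue-donation decision, so the phase can show acceptability and user experience but not decision-support effectiveness

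*Protocol article*

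**What the plan says.** Under Participant sampling and selection, the protocol article states: "An overview of the inclusion and exclusion criteria for all three phases of the study is outlined in Table 1". The one criterion in that table about the disease or the person's experience of it is "Lived experience of having a primary tumour of the brain or spine". The other criteria concern age, English, capacity to consent and digital access. None mentions a donation discussion, a donation, or a planned operation.

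The same section places recruitment on social media, charities and patient-support websites, with possible snowballing and outreach to ethnic community groups. Sample size allows at most six Phase 3 testers.

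The Objective is a tool that supports people in deciding about donation. Phase 2: build names two experience measures: CSQ-8, for satisfaction with the platform, and CollaboRATE, for how well the provider communicated about the decision. Data analysis, Phase 3, compares the Phase 3 scores statistically with the corresponding Phase 2 scores.

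Of Phase 3 itself the article says: "This phase will provide insights into the effectiveness of the intervention". The same paragraph also expects evidence towards a possible new standard of care in consent, and Data analysis, Phase 3, again describes an assessment of effectiveness.

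**The concern.** The platform is meant to help a person who has a decision to make. The entry rule lets it be tested entirely by people who have none: some may have decided long ago, and some may never have been asked. Such testers can say whether the tool is clear, usable and acceptable. They cannot show that it helped them decide, because nothing was being decided.

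What is at stake is the reading of the final phase. If the results are reported as effectiveness, or as support for changing the standard consent process, the claim goes beyond what the permitted sample can show. The CollaboRATE scores are the most exposed part. They rate a conversation with a provider, and the plan does not ensure that a Phase 3 tester has had a relevant one.

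**Working it through.** The main check is a comparison of sections; the arithmetic at the end is illustration only. The article's one calculated figure, the 45 survey participants in Phase 1a, reproduces: 1.96² × 0.03 × 0.97 / 0.05² = 44.71, rounded up to 45. This point does not depend on it. The Phase 3 maximum of six is stated, not calculated.

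**1. Who may enter Phase 3.** Table 1 covers all phases and asks for "Lived experience of having a primary tumour of the brain or spine". Someone never approached about donation meets it, and so does someone whose decision is years past.

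**2. Whether another section narrows this.** General design describes "individuals with primary craniospinal tumours who are considering or have donated tissue for research". Phase 1: explore speaks of the "lived experiences of individuals with primary brain or spinal tumours who donate tissue for research". Both are narrower than Table 1, and neither condition appears in it. Even if the first were applied as a criterion, people who have already donated would qualify, so a pending decision would still not be needed.

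**3. Whether recruitment makes a live decision likely.** No route is tied to a clinic list or a planned operation. The staged sampling is also meant to find people for the testing phase. If testers come from the survey, they reach Phase 3 only after the interview stage (follow-up within 3 to 6 months) and co-design. Someone with a decision pending at the survey may have made it by then.

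**4. What the measures refer to.** Only two experience measures are named, and Phase 3 scores are compared with their Phase 2 counterparts, so the same instruments appear to be intended. A CSQ-8 rating of the platform is meaningful for any user. A CollaboRATE rating needs an encounter about a decision. Without a current one, the tester rates memory or imagination.

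**5. What is concluded.** Effectiveness, and evidence towards a new standard of care.

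Steps 1 to 4 allow any number from 0 to 6 of 6 testers with a live decision. The conclusions in step 5 are the same whichever occurs.

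**Illustration (assumption, not in the documents).** Let q be the share of eligible volunteers with a pending decision, and treat the six testers as independent. The chance that none has one is (1 − q)⁶:

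| q | Expected number of 6 | Chance that none has a pending decision |
|---|---|---|
| 5% | 0.3 | 0.95⁶ = 74% |
| 10% | 0.6 | 0.90⁶ = 53% |
| 20% | 1.2 | 0.80⁶ = 26% |
| 30% | 1.8 | 0.70⁶ = 12% |
| 50% | 3.0 | 0.50⁶ = 1.6% |

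The table shows only how the risk varies with q. The article gives no basis for choosing a row.

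**The case against.** The strongest defence is that broad entry is deliberate and sensible. The disease is rare, the work is exploratory, and people who have been through surgery are the natural partners for co-design. General design openly includes people who have already donated. The Phase 3 text is also partly modest: it centres on user experience, satisfaction and engagement, offers insights rather than proof, and the Abstract describes the phase as refinement. Former patients can comment usefully on engagement and communication, two parts of what the article calls the primary obstacle: "the absence of effective engagement strategies, tailored communication, and appropriately timed consent processes".

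Most of this stands, and it is why no restriction of entry is asked for. It does not cover the effectiveness and standard-of-care statements, which remain in the text and need more than these testers can supply.

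A reader might go further and infer that Phase 1 is compromised because it mixes consent experiences from different eras. The article does say that practice has changed from a time when research was seldom offered, "with the decision to offer research opportunities often made solely by the treating clinician", and time since surgery is not among the comparison segments it names. But those segments are introduced as examples ("such as age groups, gender, and diagnosis"). The survey questions are in a supplement not shown here and may already record dates. Thematic analysis does not average accounts into one estimate, and the interviews leave room to place an experience in time. The documents do not support calling this a fault.

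**Conclusion.** The point holds for Phase 3. The entry rule and recruitment routes allow all of the at most six testers to be without a donation decision, past or present, while the article still plans conclusions about effectiveness and a new standard of care. Data from such testers can support acceptability and user experience. They cannot support effectiveness of decision support.

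The size is a range of what the plan permits, 0 to 6 of 6, and not an estimate. A reader might infer from the recruitment routes that most testers will be past their decision. That is plausible, but no section gives the mix, and General design expects some people still to be considering donation. The conclusion does not need that inference.

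It rests on two readings: that Table 1, though called an overview, is the operative rule for Phase 3, and that Phase 3 uses the measures named for Phase 2. If the full protocol sets a separate Phase 3 criterion requiring a pending decision, the point on who is tested falls away.

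**What to change.** 1. For each Phase 3 tester, record whether a tissue-donation decision is pending, past or was never offered, and report results by that status. With at most six people this is a descriptive listing, not a test.
2. In Phase 3: test and in Data analysis, Phase 3, limit the conclusion to acceptability and user experience. Remove the claims about decision-support effectiveness and a new standard of care.
3. Optionally, have every tester use the platform on one standard donation scenario, so that ratings refer to the same task. This standardises the exercise; it cannot reproduce the stress or time pressure of a real decision, so it does not replace step 2.
4. For Phase 1, as a suggestion only, report time since surgery or since the donation discussion alongside the themes, using existing survey items if they record it.

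The cost is one recorded item per tester, some rewording and, if chosen, a short scenario. No one is excluded and no one need be added. The real price is a narrower Phase 3 claim.
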